### Sample size considerations

#### Summative evaluation

In total, we intend to include *N* = 40 pediatricians in the study. In purpose of the planned statistical twins (matched pair approach), each group (IG, CG) should comprise *n* = 20 pediatricians.

Concerning the family sample, we calculated the sample size for the planned analyses (logistic regressions) of the primary outcome (proportion of burdened families making use of supportive services) using the software GPower. The underlying assumptions were a statistical power of 0.80 and a significance level of 5%. Concerning the effect size, we assumed that 50% of the families with psychosocial burden under treatment of IG-pediatricians would use supportive services, compared to only 10% of the burdened families of CG-pediatricians. Furthermore, we assumed that the portion of families with psychosocial burden will be about 15% in the overall sample. About 50% of the eligible families are presumed to participate in the online-survey, from which about 30% will drop out of the study up to the last follow-up measurement time-point. Thus, to detect a significant effect concerning the use of supportive services by families with psychosocial burden contrasting intervention to control group, a total of *N* = 800 families should be asked to participate by the pediatricians, namely *n* = 20 families per each pediatrician.

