### Data analysis

#### Summative evaluation

Before hypotheses are tested, we will perform dropout analyses to ascertain the amount of missing values, the mechanism of missingness and imbalances between the groups regarding study dropout and missing values. As families are treated by pediatricians, their data is not independent. Consequently, we will calculate the design effect to examine whether multilevel models should be used [26] that appear appropriate. Hypothesis are thus examined by generalized linear mixed models, in which families’ belongingness to pediatricians are accounted for by a random effect (random intercept) on Level 2. Level 1 comprises the fixed effects, with which the hypotheses are tested. The primary hypothesis will thus be tested by a multilevel binary logistic regression analysis, in which the dependent primary outcome (use of supportive services by burdened families: yes / no) is predicted by the group-variable (IG or CG) as a fixed effect on Level 1. Additionally, propensity score adjustment [27] will be applied to control for imbalances between IG and CG regarding confounding variables of pediatricians and families. The following model represents the main analysis to test our primary hypothesis:$$\mathrm{Level}\;1:\mathrm{Outcome}=\beta_{0j}+\beta_1\ast\mathrm{group}+\beta_2\ast\mathrm{propensity}\;\mathrm{score}+r_{ij}$$$$\mathrm{Level}\ 2:{\beta}_{0j}={\gamma}_{00}+{\mathrm{u}}_{0j}$$

In sensitivity analyses (SA) we will perform the main analysis without propensity-score adjustment (first SA) and as complete cases analysis (second SA). In order to consider the time taken for families to use supportive services, we will perform a time-to-event analysis that predicts the cumulative incidence of the use of supportive services by families over the three measurement points (third SA). Furthermore, we will examine if families in the IG use more supportive services than families in the CG. This explorative analysis compares the number of supportive services used by families in the IG and CG. The hypothesis on secondary outcomes will be examined analogous to the main analysis, by means of multilevel binary logistic regression analyses with propensity score adjustment.

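### The displayed main model is linear although the text says logistic, and one to one-and-a-half burdened families per pediatrician cannot support a design-effect screen or a Wald test

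*Protocol article*

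**What the plan says.** Under Data analysis (Summative evaluation), hypotheses are tested with generalized linear mixed models in which the pediatrician is "accounted for by a random effect (random intercept) on Level 2". The primary hypothesis uses a multilevel binary logistic regression, in which use of services (yes/no) "is predicted by the group-variable (IG or CG) as a fixed effect on Level 1". The equation then shown as the main analysis is, in plain notation:

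- Level 1: Outcome = b0j + b1·group + b2·propensity score + r_ij
- Level 2: b0j = g00 + u0j

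Before this, the section says: "we will calculate the design effect to examine whether multilevel models should be used". No decision threshold is given, and the next sentence moves on to mixed models as if the question were settled. Secondary outcomes are to be analysed in the same way.

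Under Sample size considerations, 40 pediatricians (20 per group) each ask 20 families, 800 in all. Half are expected to take part, "from which about 30% will drop out of the study up to the last follow-up measurement time-point", and "the portion of families with psychosocial burden will be about 15% in the overall sample". For the effect, the article assumes "50% of the families with psychosocial burden under treatment of IG-pediatricians would use supportive services"; the corresponding control figure is 10%. Power is 0.80 at the 5% level.

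**The concern.** Three things do not fit together.

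1. The prose and the equation describe different models. Read literally, the equation makes b1 a difference in proportions; the prose makes it a log odds ratio.
2. Whether a family is in the intervention (IG) or control (CG) group is fixed by its pediatrician, so group is constant within every Level 2 unit. Calling it a Level 1 effect, next to a step that might remove the pediatrician effect, leaves room for testing group as if families were independent.
3. The primary analysis uses burdened families only. If each pediatrician supplies about one such family and the control group about two users, the data say little about between-pediatrician variance, and a conventional Wald test may break down.

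At stake is the primary p-value and interval: whether they come from one model fixed in advance, and whether they remain usable when control use is as rare as the protocol expects.

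**Working it through.** **Inputs** (Sample size considerations): use 0.50 (IG) and 0.10 (CG); burdened share 0.15; participation 0.50; dropout 0.30; 40 pediatricians; 20 families asked by each. The article does not say whether the test is one- or two-sided; two-sided is assumed.

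**Step 1. Reproduce the plan's figure.** Two-proportion formula, mean proportion 0.30, no continuity correction:

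n per arm = [1.960·√(2·0.3·0.7) + 0.842·√(0.5·0.5 + 0.1·0.9)]² / 0.4² = (1.270 + 0.491)² / 0.16 = 19.4, so 20 per arm and 40 in total.

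Families to ask: 40 / (0.5·0.7·0.15) = 762, or 19.05 per pediatrician. Rounding up to 20 gives 20·40 = 800. The plan's N is reproduced, with no allowance for clustering.

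**Step 2. Families in the primary model.**

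| | Completers only | Dropouts kept |
|---|---|---|
| Burdened families | 800·0.5·0.7·0.15 = 42 | 800·0.5·0.15 = 60 |
| Per arm | 21 | 30 |
| Per pediatrician | 1.05 | 1.5 |
| Expected control users | 2.1 | 3.0 |

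Both columns matter, because the article lists complete cases only as a sensitivity analysis.

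**Step 3. Equation against prose.** A binary logistic mixed model has logit P(Y=1) on the left and no additive residual. The display has the raw outcome and r_ij. They are different models.

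**Step 4. Level of group.** Substituting Level 2 into Level 1 as displayed gives g00 + b1·group + b2·PS + u0j. With group at Level 2 it gives g00 + g01·group + b2·PS + u0j. The linear predictor is the same, so no estimate changes while u0j is present.

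**Step 5. Information on the pediatrician variance.** With burdened completers per pediatrician distributed as Binomial(20, 0.0525), the probabilities of none, one, and two or more are 0.340, 0.377 and 0.283. Of 40 pediatricians, that is 13.6, 15.1 and 11.3. Only about 11 can inform the within-pediatrician correlation (about 18 if dropouts are kept).

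A simulation of 600 trials per setting on completers assumed a true random-intercept SD of 0 or 0.6 on the logit scale; the article gives no value. In trials with at least one control user, the SD was estimated as zero in 59% and 52% of fits respectively, and above 3 in about 8% of fits in both settings. The estimate hardly distinguishes no clustering from moderate clustering.

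The size-weighted mean cluster size is (0.995 + 1.05²)/1.05 = 2.0, so the design effect is 1 + (2.0 − 1)·ICC: 1.01, 1.05 and 1.10 for assumed ICCs of 0.01, 0.05 and 0.10.

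**Step 6. Control users and the test.** P(no control user) = 0.9²¹ = 0.109, or 0.9³⁰ = 0.042. With none, the estimated odds ratio is infinite and the Wald statistic is useless. The table gives exact enumeration over all 2×2 outcomes, without propensity score or clustering. Tables without a finite odds ratio count as non-significant for Wald. Firth adds 0.5 to each cell and uses the penalised likelihood ratio.

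| | 21 per arm | 30 per arm |
|---|---|---|
| Power, Wald | 73% | 90% |
| Power, Fisher | 76% | 91% |
| Power, likelihood ratio | 86% | 96% |
| Power, Firth | 84% | 95% |
| Type I error at 10% vs 10%, likelihood ratio | 8.5% | 7.5% |
| Type I error at 10% vs 10%, Firth | 4.1% | 4.1% |

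**The case against.** The strongest reply is that the prose settles the model. It says generalized linear mixed model, and it says binary logistic for both the primary and the secondary outcomes; the sample size section also speaks of logistic regressions. A reader might infer that a linear model will be fitted and a risk difference reported. The article never mentions a risk difference, and the display is better read as a notation error. That stands, but the equation is labelled as the main analysis and should be corrected.

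A reader might also infer that putting group on Level 1 biases its effect. Step 4 shows that it does not.

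A third tempting inference is that the model cannot be fitted, or that the trial has only 73% power. Neither is supported. A zero variance estimate turns the model into ordinary logistic regression, which is a usable result. The 73% needs both a Wald test, which the article does not specify, and a completers-only analysis, which it treats as a sensitivity analysis. At 30 per arm Wald power is 90%. The 15% burdened share may also be low: the Background gives 12.9% with four or more risk factors, while the study threshold is three or more.

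Finally, the sentence after the design-effect step commits to mixed models, and the choice of test and fallback rules often sit in an analysis plan that is not shown. The absence of those rules is therefore not the finding. What remains is that the article states a screening step that these data cannot inform, and that the expected counts make the choice of test consequential.

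**Conclusion.** The point holds in a limited form. The displayed equation contradicts the named model and needs correcting; the Level 1 label for group is a mislabelling without numerical effect as long as the random intercept stays. The design-effect step should not decide the primary model: about 11 of 40 pediatricians are expected to contribute two or more burdened completers, and allocation is by pediatrician whatever the estimate shows.

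The fragility of a Wald test ranges from material at 21 per arm (11% chance of no control user, power 73%) to modest at 30 (4%, power 90%). These figures rest on the protocol's 50% and 10% use, 15% burdened share, 50% participation and 30% dropout, and they ignore the propensity score and clustering. The simulated variance results also rest on an assumed random-intercept SD.

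**What to change.** 1. Replace the displayed model by logit P(Y_ij = 1) = b0j + b2·PS, with b0j = g00 + g01·group_j + u0j and no r_ij.
2. Delete the design-effect screen. Always keep the pediatrician random intercept and accept a zero variance estimate if it occurs. The design effect can still be reported descriptively.
3. Prespecify a Firth-type penalised test and interval for the group effect. It is preferable to a plain likelihood-ratio test, whose unadjusted type I error is about 8% at 21 per arm with 10% use in both groups, and it stays finite when there are no control users.
4. Apply the same wording to the secondary outcomes that inherit the model.

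A model on all surveyed families with a group-by-burden interaction could be added as a sensitivity analysis. It would steady the variance estimate but assumes a common pediatrician variance and propensity-score slope for burdened and non-burdened families, so it is not required.

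The cost is a change of wording before the analysis, slightly non-standard software for a penalised mixed model, and possibly a wider interval. No new data are needed.

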#### Process evaluation

##### Cost-effectiveness analysis

The cost-effectiveness of the PATH-intervention will be analyzed by calculating incremental cost-effectiveness ratios (ICERs) for the following primary and secondary outcomes:Additional costs per use of supportive services by families with psychosocial burden.Additional costs per correctly identified family with psychosocial burden by the pediatrician.Additional costs per additional informing of an identified family by the pediatrician about regional supportive services and motivating them to use these services.

All ICERs will be determined separately from the healthcare and societal perspective and 95% confidence intervals will be calculated based on Fieller’s theorem [28].

##### Analysis of the interviews

The transcribed interviews of families are analyzed using the method of content structuring according to the qualitative content analysis by Kuckartz [29]. For this purpose, all data material is categorized and coded.

Prior studies [7, 10] already provide evidence in the areas of interprofessional collaboration, referral of families to the ECI network and utilization of supportive services. On this basis, and framed by the interview guidelines, an initial coding system will be deductively developed in advance. Based on this initial coding system and themes emerging from the interviews, the categories will be inductively differentiated and specified. Two researchers will carry out these analyses and the intercoder consistency will be evaluated.

Interviews of IG pediatricians and ECI network members will be analyzed by a category-based approach or, depending on data material, with other appropriate methods (e.g., summarized descriptions, case-by-case analysis).

With the content structuring of the material available, category-based, topic-oriented evaluations can be carried out in the further analysis, i.e. how often, or for how many persons, a content-related category (or also a category combination) was coded, and how categories/topics are related. The presentation of results can then be based on summary descriptions supported by meaningful quotations.

##### Analysis of the observation

Treatment fidelity of the complex intervention will be analyzed in a three-step procedure, which will be conducted independently by two researchers and subsequently brought together. First, we document the topics discussed concerning the family’s burden, psychosocial issues, living conditions and the family’s resources, as well as in regard to supportive services. For that, we use a systematically developed schedule, which comprises aspects of the PATH-intervention. For example, the schedule includes aspects of the interview guide, which pediatricians should use in the case of uncertainty about the extent of the family’s psychosocial burden. We record the discussed topics and complement this with the information of the researchers’ observations such as facial expressions and gesture. Additionally, the table includes whether the discussed topic is marked as concern or distress, either by the pediatrician or by parents.

Secondly, we focus on the pediatrician’s conversation style and prevention-promoting attitude, which are core elements of the PATH-intervention. Thus, we rate the conduction of the parental conversation and consultation by using the two central dimensions of Motivational Interviewing, *partnership* and *empathy* [30]. Partnership describes the extent of participatory involvement of parents and the shared expert roles of the pediatrician on the one hand, and parents on the other [30]. Empathy represents the pediatrician’s efforts to understand the parental perspective and to reflect this understanding to the parents [30].

The third step is a conversation analysis of the documented conversation passages of step 1. This analysis focusses on the way the topics are discussed e.g. active listening, appreciation, repeating and summarizing the parents’ contributions. In this step, we categorize different types of questions [31] used by the pediatrician in terms of the extent of evocation of parental perspectives. We expect that pediatricians of the intervention group prefer using open questions and narrative (follow-up) questions for this purpose, based on the skills learned in the one-day training program of the PATH-intervention [32]. Furthermore, a balance index [33] will help to evaluate how often the contributions of the pediatrician refer appropriately to the parents’ contribution and vice versa.

Table 1 displays a summary of the outcomes, measurements, data source and measurement time-points, as well as methods of analysis.

**Table 1 Tab1:** Summary of outcomes, measurements, data source and measurement time-points, and methods of analysis

Outcomes	Measurement	Data source	Measurement time-point			Data analysis
			t1	t1	t2	
Use of supportive services by families with psychosocial burden (primary outcome)	Online-survey	Families	x	x	x	Comparison of intervention & control group using generalized linear mixed models
Correctly identified families with psychosocial burden (secondary outcome, proximal)	Paper-pencil-questionnaire	Pediatricians	x			
Information provision & motivation of families with psychosocial burden by the pediatrician (secondary outcome, proximal)	Online-survey	Families	x	x	x	
Cost-effectiveness ration of the PATH-intervention (secondary outcome, distal)	Direct costs of the intervention, health insurance claim data	Association of Statutory Health Insurance Physicians Baden-Wuerttemberg, Statutory Health Insurance “AOK” Baden-Württemberg	Throughout the study.			Calculation of incremental cost-effectiveness ratios (ICERs)
Acceptance of the PATH-intervention (secondary outcome, distal)	Telephone interviews	Families with psychosocial burden, IG-pediatricians, ECI network members	Throughout the online-survey data collection phase.			Qualitative content structuring
Treatment fidelity	Video-assisted observations	IG-Pediatricians	The next preventive medical check-up (U4-U6) of a participating family with psychosocial burden.			Qualitative analysis (incl. Conversation analysis)

Note: t1/ t2/ t3 = first/ second/ third measurement time-point; “U” = U-Untersuchung (preventive medical check-up for children aged 0-3 years)

## Discussion

Representative studies showed that about 13% of the families with small children (aged 0 to 3 years) visiting a pediatrician for a preventive medical check-up have considerable risk factors [7, 5]. Such risk factors increase the probability for psychosocial burden in the family and the vulnerability to severe developmental consequences for the child, making early interventions urgently necessary. In this context, supportive services for burdened families can be beneficial. Although supportive services of the ECI are implemented nationwide, families with psychosocial burden rarely attend these services. The PATH-intervention therefore aims at training the pediatricians’ skills to facilitate the communication with burdened families with small children and the referral to tailored supportive services. Using a prospective quasi-experimental, controlled (matched-pair), longitudinal mixed-method design, we evaluate the target accuracy of this complex healthcare intervention. Quantitative data will allow us to evaluate the extent to which the intervention enables the pediatricians to identify and recommend supportive services to burdened families, and the families’ use of the supportive services of the ECI. Moreover, health-economic analysis will show the cost-effectiveness ratio of the PATH-intervention. Qualitative data will enable us to get a deeper insight into the subjective evaluation and acceptance of the PATH-intervention in the perspective of all the stakeholders involved, as well as in the pediatricians’ treatment fidelity in daily routine care.

By exploring the successful identification of burdened families, recommendation and usage of supportive services, this study could be a starting point for future research. Moreover, the results of this study could form the basis for the broader implementation of the PATH-intervention as standard care.

Nevertheless, some limitations of the study should be mentioned. The evaluation is restricted to two structurally similar German states. Thus, the results may be influenced by specific characteristics of these two states, e.g. their relatively high economic performance. Furthermore, due to an initial briefing session to recall the intervention contents and the selective observations in the IG, as well as due to the study participation itself, it is unavoidable that the pediatricians are sensitized to the issue of families’ psychosocial burden. Therefore, it is possible that the pediatricians will act in a different manner to usual under study participation conditions.

## Conclusion

In summary, due to the great relevance of families’ risk factors and psychosocial burden for both the individual family and the developing child, as well as from a social and economic point of view, this study contributes to an important research field. The results of this study could form a starting point not only for further research, but also for the broader implementation of the PATH-intervention as standard care. The latter could prospectively contribute to the enhancement of the care situation for burdened families with small children.

## Data Availability

Not applicable.

## Abbreviations

PATH: Pediatric Attention To Help
ECI: Early Childhood Intervention Program
U1 up to U9: “U-Untersuchung”, medical check-up for infants
NZFH: National Center for Early Prevention
CHWS: Child and youth welfare services
IQCs: Interprofessional Quality Circles
IG: Intervention Group
CG: Controll Group
PHQ: Patient Health Questionnaire
SA: Sensitivity analyses
ICERs: Incremental cost-effectiveness ratios
